## Abstract

**Introduction:**

Strong primary healthcare enhances resource efficiency and resilience. Type 2 diabetes poses a growing global health challenge, with Argentina’s healthcare system struggling to detect and manage the disease effectively. Many patients bypass primary healthcare for secondary facilities, undermining continuity of care and increasing costs. Following a diagnostic process in collaboration with policymakers, we propose evaluating a redesigned primary care model consisting of codesigned evidence-based implementation strategies to improve type 2 diabetes management in Mendoza, Argentina.

**Methods and analysis:**

This is an efficient, parallel-arm cluster randomised controlled Hybrid Type II trial with 12 clusters (administrative areas with 2–3 health facilities) allocated 1:1 to control (usual care) or intervention. In phase I, we will codesign, pilot and refine an implementation strategy package. In phase II, we will conduct the trial: 9-month baseline data collection, 15-month intervention and 6-month sustainability period. We will enrol a cohort of 396 patients with type 2 diabetes at primary healthcare centres and follow them for 12 months during the intervention and 6 months sustainment using routine clinical records and patient surveys. In phase III, we will conduct analysis, report and disseminate findings. The primary outcome will be a composite outcome including glycaemic control (glycated haemoglobin (HbA1c) <8%); blood pressure control (<140/90 mm Hg) and statin prescription (limited to patients ≥40 years) from clinical records. The primary analysis will compare the proportion of patients achieving this composite clinical outcome between the trial arms at the end of the study. Secondary analyses include assessing patient experience and primary healthcare engagement; testing the implementation strategies’ impact on service use patterns, system competence, user confidence and cost per visit; exploring inequalities by sociodemographic factors; and assessing patient empowerment. We will use all available data from all randomised clusters and conduct all analyses on the intention-to-treat population, regardless of intervention adherence.

**Ethics and dissemination:**

All study activities will comply with national and international ethics guidelines, presenting minimal risk to participants. The protocol was submitted and approved by the local independent ethics committee at the Mendoza Ministry of Health (Consejo Provincial de Evaluación ética en investigación en Salud-Provincial Health Research Ethics Review Board, Reference number: 149/2024). Facility-level permission will be obtained for participation and sharing of deidentified data. Written informed consent will be required from study participants, who will receive information on the study’s purpose, procedures, risks and benefits. Dissemination activities and outputs will include writing and submitting manuscripts for publication; writing policy briefs to support strategy implementation in other regions or countries; and tailoring outputs for patients, clinicians and researchers. We anticipate that improvements in disease management and patient experience will have clinical and economic benefits related to reduced usage of secondary-level and tertiary-level facilities, lower cost per visit and a reduced number of clinical events related to diabetes.

**Trial registration number:**

ISRCTN63277390.

STRENGTHS AND LIMITATIONS OF THIS STUDYThis study integrates the Implementation research logic model and the normalisation process theory to support the design and evaluation of strategies. This dual framework approach enhances our capacity to understand whether the strategies improve care and how and why they do so in complex, real-world settings.The inclusion of community engagement throughout all phases of the study aims to ensure relevance and enhance the sustainability of the strategies to be implemented.As far as we know, this study will be among the first cluster randomised controlled trials in Latin America to evaluate the implementation of a co-designed care model for chronic diseases in the public primary healthcare system.Implementing this study in an Low- and middle-income countries (LMIC) is complex and influenced by dynamic factors such as political shifts, workforce constraints, competing policy priorities and resource limitations.Findings from a single province in Argentina may have limited generalisability to other settings without careful adaptation to local health system structures and sociocultural dynamics.

## Introduction

 Strong primary healthcare (PHC) saves lives, improves resource use efficiency and makes health systems more resilient and effective for the population.^1^ Functional PHC systems should be able to prevent and detect prevalent and impactful non-communicable diseases (NCDs) such as diabetes and to manage ongoing diseases.^2^ Service delivery redesign (SDR) is an innovative, system-level framework for improving care delivery defined as the reorganisation and strengthening of existing services and care pathways to maximise quality care and optimise health outcomes.^3^

Latin American countries have been at the forefront of achieving universal health coverage for their populations and working to provide equitable person-centred care.^4^,^6^ However, health system quality in this region is inadequate to deliver on the promise of universal health coverage, resulting in incomplete detection, insufficient control of chronic conditions and high out-of-pocket costs.^7^ There are also a few systematic efforts to give patients a voice about their opinions and experience with the care they receive.^8^ Argentina, an upper-middle-income country in Latin America, has a primarily publicly financed health system: 60% of the population is covered by the social security sector run by labour unions and at least 36% by government healthcare, with the remaining 4% covered by private insurance.^9^ Dependence on public healthcare will only continue to increase as economic turmoil fuels rising unemployment.

Type 2 diabetes mellitus (T2D) is an increasing global health burden. In 2019, diabetes was the direct cause of 1.5 million deaths worldwide.^10^ In addition to the cost of treatment for T2D and its complications, which is a significant burden for national health services, T2D and other NCDs heavily impact productivity, particularly concerning lost or reduced working days due to illness.^11^ Central and South American countries spend an average of 18.4% of their total health expenditure on diabetes.^12 13^ Diabetes detection and control are primarily the responsibility of the non-private schemes.^14 15^ To date, Argentina’s PHC system has failed to meet this challenge; T2D detection and control coverages are low, and those in treatment often bypass PHC for secondary facilities.^16^ Of the estimated 12.7% of the national population living with T2D, only 50% are aware of living with their diagnosis, and only 40% of these individuals have achieved metabolic control (HbA1c <7%), leaving 80% of cases uncontrolled.^17 18^

The Quality Evidence System Transformation Network (QuEST Network) provides policymakers with evidence and tools for health system improvement. QuEST-Latin America and the Caribbean leads regional research and dissemination.^19^ Collaboration with the government of the Argentinian province of Mendoza led to efforts to address post-COVID-19 health challenges. Together, we conducted a comprehensive assessment of PHC system quality, focusing on NCDs and patient experience. This diagnostic assessment included a population-based survey of 1220 respondents, a cohort study of patients with diabetes, analysis of routine health data to identify care patterns and disease control, and qualitative studies of how NCD patients use PHC services and how providers interact with these patients.^16 20^ Our analysis from this diagnostic process showed significant deficits in patient experience, system competence and trust in the public health system. The study found that accessing care was difficult due to appointment difficulties and long waiting times, and obtaining medication and laboratory tests at secondary centres was also problematic. Financial constraints were significant, with co-payments in the social security sector, transportation costs and lost work revenue. Strategies employed included networking, emergency service use, careful planning and taking loans.^16^ We also conducted a Delphi consensus process with local stakeholders to identify specific recommendations, based on the findings of the diagnostic studies, to improve healthcare services.^21^ Based on this diagnostic process and our established relationship with policymakers and stakeholders in the province of Mendoza, we propose to codesign a new model of care to be tested and evaluated in a pragmatic cluster randomised controlled trial to improve health for individuals with diabetes in Argentina.

In this protocol, we conceptualise the redesigned PHC model itself—built around the national clinical guideline for T2D management—as the core intervention. Our trial tests a package of implementation strategies designed to embed this guideline-based model into everyday practice.

## Methods and analysis

### Aims

The primary objective is to improve disease control in individuals with T2D. Secondary objectives are (a) to improve the care experience, (b) to assess the feasibility and acceptability of the redesigned model and its implementation package, (c) to test the model’s impact on service use patterns, system competence, user confidence and cost per visit and (d) to analyse the impact of the model on potential inequalities by sociodemographic factors.

### Design

This study is a pragmatic, parallel-arm, cluster-randomised controlled Hybrid Type II trial. 12 provincial health and administrative departments, each comprising 2–3 PHC centres—clusters—will be randomised in a 1:1 ratio to either the intervention or control (usual care) arm (figure 1). The trial will be conducted over 36 months and organised into three overlapping phases (figure 2). Phase I (9 months): Codesign, pilot testing the PHC care model’s refinement and associated implementation strategies. This phase will involve a pilot in two PHC centres, identification of barriers and iterative adaptation of the strategies. Phase II (30 months): Implementation of the trial. This phase includes a 9-month baseline data collection period, a 15-month intervention implementation period, and a 6-month follow-up in the intervention group to assess the sustainability of the implementation strategies. Phase III (6 months): Analysis, reporting and dissemination of findings. The study started on 1 November 2024 and ends on 31 October 2027.

**Figure 1 F1:**
[figure not shown]
CONSORT flow diagram. CONSORT, Consolidated Standards of Reporting Trials.

**Figure 2 F2:**
[figure not shown]
Study overview. QILN, Quality Improvement Learning Network; RCT, randomised controlled trial.

### Patient and public involvement

Community engagement (CE) will be integral to the study. CE is defined as a process of inclusive participation that promotes genuine partnerships among individuals and groups who share geography, interests or experiences, with the aim of addressing issues affecting community well-being.^22^,^24^ This approach is not only ethically imperative but also instrumental in building trust, enhancing participation and promoting the acceptability and uptake of research findings. Four stakeholder workshops will be held annually throughout the study to support CE. These will involve patients, community representatives, healthcare providers and decision-makers. The workshops will serve as a platform to review study progress, promote inclusive dialogue and ensure that the research remains aligned with community needs and priorities. A CE coordinator will facilitate these sessions, with particular attention to the perspectives of underserved populations who experience barriers to healthcare. Workshops will take place in PHC centres and incorporate structured facilitation techniques to encourage diverse participation and equitable voice. Additionally, a stakeholder advisory committee—comprising a community liaison, a social worker and representatives from participating PHC centres—will oversee and guide CE activities. This committee will provide feedback on the implementation process, monitor the responsiveness of the intervention to community input, and contribute to the long-term sustainability of the model of care.

#### Phase I: codesigning and piloting the care model and its implementation strategies

The purpose of this phase is to codesign a PHC care model and its associated implementation strategies to be tested in a cluster randomised controlled trial, aiming to improve disease management and care experience in patients with T2D. Figure 3 shows the flow chart of this phase.

**Figure 3 F3:**
[figure not shown]
Phase I: model design, refinement and pilot testing.

We define the intervention as the guideline-driven PHC care model for diabetes, and implementation strategies as the theory-informed activities that will support integration of that model into routine practice.

##### Theoretical framework

The study will be guided by three complementary frameworks: the implementation research logic model (IRLM), normalisation process theory (NPT) and principles of CE.

The IRLM will be used to structure the design and evaluation of the implementation strategies. This framework maps the relationships between context-specific determinants, selected implementation strategies, mechanisms of action and outcomes.^25^ It will support a systematic approach to identifying barriers and facilitators, selecting appropriate strategies and articulating how these are expected to produce change. The IRLM is grounded in three core principles: (a) implementation strategies must be tailored to the specific context, (b) strategies operate through distinct mechanisms and (c) implementation outcomes, shaped by these mechanisms, ultimately influence clinical outcomes.^22^

The NPT will complement the IRLM by offering an explanatory lens to understand the processes through which the codesigned care model and its associated implementation strategies become embedded in routine practice.^26^ NPT will be used during the codesign phase to identify factors that may affect stakeholder engagement and operationalisation of implementation strategies.^27^ It will also guide the evaluation of implementation processes. NPT posits that complex interventions are normalised through collective action and shared sense-making. The theory highlights four key constructs: coherence (how stakeholders make sense of the intervention), cognitive participation (engagement and commitment), collective action (how the work is enacted) and reflexive monitoring (ongoing appraisal and adaptation).^26 28^ These constructs will be used to examine how individuals and teams integrate the intervention into existing workflows and cultures. Together, IRLM and NPT will ensure that the development, deployment and evaluation of the implementation strategies are grounded in both theory and context.

##### Procedures

The codesign process will be structured through a series of workshops aimed at developing a new care model for improving diabetes care in PHC settings. The workshops will be held in a venue provided by the Ministry of Health, ensuring a conducive and collaborative environment. A multidisciplinary team, including researchers, a psychologist, a social worker and a drama teacher, will facilitate the sessions. Participants will include patients, healthcare professionals and policymakers, who will be grouped to encourage diverse perspectives in discussions. The workshops will involve interactive activities such as role-playing and user journey mapping to identify barriers and facilitators in diabetes care. The final sessions will focus on prioritising solutions using the IRLM, and then participants will finalise the implementation strategies, ensuring feasibility and alignment with available resources.

##### Piloting the PHC care model and its associated implementation strategies

The PHC care model package will be tested and piloted in two facilities selected by the research team and study advisors, meeting the eligibility criteria for the effectiveness trial but will not be included in the trial. The pilot will last for 4 months. The PHC centre director will organise a team that includes physicians, nurses and a representative from a patient group. We will implement co-designed strategies and monitor the implementation. Throughout the pilot, we will conduct on-site evaluations and surveys with patients and providers to assess the acceptability of the model. After the pilot, we will conduct an implementation evaluation through two focus groups with patients from the participating sites and eight in-depth interviews with healthcare providers to investigate patients’ and providers’ experiences with the implementation, fidelity, acceptability and feasibility. Information obtained through the triangulation of data collected through on-site evaluation, clinical records, surveys, focus groups and interviews will address the implementation outcomes of feasibility, fidelity and acceptability.^29^ Qualitative data from focus groups and interviews will be used to describe the experience and identify the challenges in implementing the model and its strategies. In preparation for the implementation trial, we will refine the model structure, manualised procedures, needed resources and training materials, and finalise data collection tools. As part of the first phase of this study, we will conduct an implementation mapping exercise, systematically linking each strategy to the determinants identified during our diagnostic studies using the Expert Recommendations for Implementing Change (ERIC) taxonomy. These mappings will be captured in our IRLM and refined iteratively, ensuring that every activity directly addresses a known barrier to normalisation.

### Phase II: trial deployment

#### Setting

The trial will be implemented in PHC centres across the province of Mendoza, Argentina, which serve approximately 45% of the population, primarily individuals from socioeconomically disadvantaged backgrounds. The province is administratively divided into 18 departments. The unit of randomisation (cluster) will be the department. 12 departments will be selected, each contributing at least two PHC centres. Clusters will include two or three PHC centres providing care to ≥50 individuals diagnosed with T2D per cluster. Centres involved in the pilot phase will be excluded from phase II.

#### Study participants

The study population will include adult patients with T2D who receive care through the public healthcare system. Eligibility criteria are age ≥18 years, a confirmed diagnosis of T2D for at least 1 year, residency in Mendoza province and receipt of care at one of the participating PHC centres. We will construct a longitudinal cohort of 396 patients with T2D in both arms, enrolling patients before implementation and following them for 12 months for outcome assessment (e-Cohort).

#### Sample size

Based on preliminary data from the diagnostic phase and published literature, the baseline rate of achievement for the composite primary outcome (glycaemic control (HbA1c <8%); blood pressure control (<140/90 mm Hg); and use of statins (statin prescription) -limited to patients ≥40 years-) in the control group is estimated at 30%. The intervention is expected to improve this to ≥50% (absolute effect size of 20%). We have calculated the sample size considering a parallel cluster randomised trial with a cohort design, including baseline and follow-up assessments. The trial is powered at 80% to detect an absolute difference of 20 percentage points between the control group (30%) and the intervention group (50%) on the composite primary outcome, assuming a two-sided significance level of 5%. The design includes six clusters per arm (12 in total) and accounts for the correlation structure of repeated measures using a two-period decay model. Specifically, we assumed an intracluster correlation coefficient (ICC) of 0.05, a cluster autocorrelation of 0.5, and an individual autocorrelation of 0.6. Standard errors were adjusted using a t-distribution to account for the small number of clusters. Based on these parameters, the required sample size before adjusting for attrition is 312 individuals (26 per cluster). Applying an attrition inflation factor of 1.25 (to allow for 20% loss to follow-up), the final sample size increases to 396 individuals (33 per cluster, 198 per arm).

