#### Data analysis

We will use all available data from all randomised clusters and conduct all analyses on the intention-to-treat (ITT) population, including all clusters and patients in the randomised group, regardless of intervention adherence. Summary statistics will be given for baseline data by treatment group using means, SD, medians, minimum, maximum and quartiles for continuous variables and counts and percentages for categorical variables. We will quantify complete vs incomplete records and describe the characteristics of patients lost to follow-up.

For the composite clinical outcome, the primary ITT analysis will compare the proportion of patients achieving an HbA1c level <8%, blood pressure control <140/90 mm Hg and statin uptake between the trial arms at the end of the study. We expect a good covariate balance between the groups; therefore, the ITT analysis will be performed by comparing proportions. Patient and cluster-level covariates can be included in a mixed-effects logistic regression model to account for the cluster effect and obtain an adjusted estimate of the average treatment effect for within-cluster change.^35^ Adjusted ORs will be reported with 95% CIs, p values and ICCs will be reported to estimate the percentage of variance explained by each level.

For quality of care, we will compare the proportion of patients reporting overall quality of care as ‘excellent’ or ‘very good’ before and after the intervention phase between trial arms using difference-in-difference regression analysis to estimate the average treatment effect. Engagement and confidence in the health system will be evaluated by comparing the proportion of patients achieving the expected threshold in each trial using a χ^2^ test for proportions. Fisher’s exact test will evaluate system competence across participating PHC centres. Direct costs related to diabetes care will be reported for each group. We may expect higher costs in the intervention group due to increased and better utilisation of health services. The mean cost will be analysed considering the variable distribution (non-normal/normal). For all outcomes, we will conduct mixed effects regression adjusted for covariates and clustered by department to provide an average treatment effect for expected change in outcomes within each department.

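### The 80% power takes credit for the baseline measurement, but the stated primary analysis is an endline comparison of proportions; a valid cluster-adjusted version of it has about 58-73% power

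*Protocol article*

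**What the plan says.** The Sample size section of the protocol article describes "a parallel cluster randomised trial with a cohort design, including baseline and follow-up assessments" and states that the calculation "accounts for the correlation structure of repeated measures using a two-period decay model". The correlation inputs are given in one sentence: "we assumed an intracluster correlation coefficient (ICC) of 0.05, a cluster autocorrelation of 0.5, and an individual autocorrelation of 0.6". A t-distribution is used because clusters are few, but its degrees of freedom are not given. With six departments per arm and rates of 30% and 50%, the requirement is 26 per department (312), raised to 33 (396) for 20% attrition. On this basis, "The trial is powered at 80% to detect an absolute difference of 20 percentage points".

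The Data analysis section defines the primary analysis of the composite as a comparison of HbA1c control, blood pressure control and "statin uptake between the trial arms at the end of the study". It says that this will be done by comparing proportions, because good covariate balance is expected. A mixed-effects logistic model with covariates is offered as something that can be done, and adjusted mixed models clustered by department are promised for all outcomes. The same section uses baseline explicitly for user-reported quality of care, "using difference-in-difference regression analysis to estimate the average treatment effect", but has no such statement for the composite. The Randomisation procedures section makes covariate adjustment conditional on residual imbalance. Missing clinical outcomes are counted as not achieving the composite.

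**The concern.** The sample size and the primary analysis describe two different estimators. Cluster and individual autocorrelation measure how well baseline predicts endline, for departments and for patients. They shrink the variance of the treatment effect only when the analysis uses the baseline outcome. A comparison of endline proportions does not use it, however well balanced the arms are: balance concerns chance differences between arms, not residual variance.

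Two things are at stake. If the endline comparison is done with proper allowance for clustering, its power is well below the stated 80%. If it is done as a plain comparison of proportions, clustering is ignored and the type I error is inflated. With only 12 departments, the trial can afford neither.

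**Working it through.** **Inputs (Sample size section).** Rates 0.30 and 0.50; two-sided 5%; 6 departments per arm; m = 26; ICC 0.05; cluster autocorrelation (CAC) 0.5; individual autocorrelation (IAC) 0.6. Not stated, so varied here: degrees of freedom (df) and variance formula.

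**Formulas.**
- Design effect: DE = 1 + (m − 1) × ICC = 1 + 25 × 0.05 = 2.25.
- Correlation of a department's baseline and endline means: r = [m × ICC × CAC + (1 − ICC) × IAC] / DE = (0.65 + 0.57) / 2.25 = 0.542.
- Variance multiplier from using baseline: 1 − r² = 0.706.
- SE = √[V / (6m) × DE × k], with k = 0.706 if baseline is used and k = 1 if it is not. V is 0.30 × 0.70 + 0.50 × 0.50 = 0.46 (unpooled), 2 × 0.40 × 0.60 = 0.48 (pooled) or 2 × 0.30 × 0.70 = 0.42 (control-arm rate in both arms).
- Power from the noncentral t with noncentrality 0.20/SE, or the normal distribution where marked.

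**Step 1: the plan's own figure.** With baseline used and unpooled variance, SE = √(0.46/156 × 2.25 × 0.706) = 0.0684. Power is 79.6% on 21 df, 79.8% on 22 df and 80.1% on 24 df. The stated 80% therefore reproduces when the baseline outcome is in the estimator. The attrition step is also right: 26 × 1.25 = 32.5, rounded up to 33, and 33 × 12 = 396.

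**Step 2: the stated primary comparison, with clustering allowed for.** Endline only, unpooled: SE = √(0.46/156 × 2.25) = 0.0815.

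| Endline only, m = 26 | 10 df | 22 df | Normal |
|---|---|---|---|
| Unpooled (0.46) | 60.1% | 65.1% | 69.0% |
| Pooled (0.48) | 58.3% | 63.2% | 67.1% |
| Control-arm (0.42) | 64.0% | 69.0% | 72.9% |

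No cell reaches 80%. On 10 df with unpooled variance, 80% would need 241 per department.

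**Step 3: the literal reading.** A plain two-proportion test ignores a design effect of 2.25, so its statistic has a standard deviation of √2.25 = 1.5 under the null. Type I error = 2 × [1 − Φ(1.96/1.5)] = 19%.

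**Step 4: baseline used, df taken as 12 − 2 = 10.** At m = 26, power is 75.0% (unpooled), 73.2% (pooled) or 78.7% (control-arm). With unpooled variance, 80% needs 38 per department.

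**Step 5: missing outcomes counted as failures.** Up to 33 per department are then analysed, giving DE = 1 + 32 × 0.05 = 2.6. With rates unchanged, 10 df and unpooled variance, power is 64% endline-only and 78% with baseline. If, as an assumption, 20% are missing in each arm, the rates become 0.8 × 30% = 24% and 0.8 × 50% = 40%, and power is about 49% and 63%.

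**The case against.** The best defence is that the article does foresee models that could use baseline. It speaks of a treatment effect for within-cluster change and promises adjusted mixed models for every outcome. The covariate list may well be in an analysis plan that is not shown. This stands in part: it cannot be said that the trial will never use the baseline composite. But the article itself fixes which comparison is primary, and that comparison is not the one that the power figure assumes. This is a mismatch between two stated things, not an omitted detail.

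Three stronger readings are tempting and not supported.
- A reader might infer that the power was computed on 21-22 df, wrongly treating both periods' department means as independent. The article gives no df. On 21-22 df the result falls just short of 80%, and 10 df with control-arm variance gives 78.7%, also a near match. The df used cannot be identified.
- A reader might infer that the planned test simply has 60% power. That figure belongs to a cluster-adjusted endline test on 10 df, which the article does not spell out. Read literally, the comparison errs towards false positives instead.
- A reader might count the difference-in-differences analysis of quality of care as part of the fault. It is a valid analysis of a secondary outcome for which no power is claimed, so it is not.

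**Conclusion.** The mismatch holds. The 26 per department rests on a variance multiplier of 0.706 that the stated primary comparison does not earn. Under the plan's own rates and correlations, a valid endline-only test at 26 per department has about 58-73% power (60% on 10 df with unpooled variance), and a test that ignores clustering has about 19% type I error. The conclusion that 80% is not reached endline-only does not depend on the choice of df or variance formula. Whether the stated 80% is also optimistic for a baseline-adjusted analysis does depend on that choice: on 10 df power would be 73-79%. All figures assume that the ICC and both autocorrelations are as stated; step 5 shows how far the rule for missing outcomes could move them.

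**What to change.** In the Data analysis section, make the primary test a mixed model of the endline composite on arm, with a random department effect, the patient's baseline composite as a covariate and a small-sample df correction. Comparison of raw proportions can stay as description.

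In the Sample size section, state the df and the variance formula used. If these are 12 − 2 = 10 df and unpooled variance, restate power as about 75% at 26 analysed per department (73-79% across variance formulas). Add that counting missing outcomes as failures changes both the number analysed and the expected rates, and give power under that rule. If the endline comparison is kept as primary, it must allow for clustering, and its own power should be stated.

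The cost is wording and one recalculation, settled before endline data are seen. The sample size already presupposes a baseline assessment, so no extra patients or visits are needed. The price is a possibly less favourable stated power.
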